### Objectives and major research questions

The primary purpose of this study is to expand the research on self-guided internet interventions for disordered gambling and explore whether they can have a more pronounced benefit when paired with minimal supportive clinician contact provided digitally. This contact will come in the form of motivational interviewing, which has been successfully paired with bibliotherapy in multiple prior trials [12–14] but has yet to be paired with online self-directed interventions for problem gambling. The specific objectives are twofold: (1) replicate, in the context of virtual care, the finding that supplemental motivational enhancement improves self-directed gambling treatment outcomes; and (2) test the hypothesis that supplemental motivational enhancement increases online self-help treatment adherence and engagement of individuals seeking treatment for gambling problems.

The current study will randomly assign participants to one of two conditions: internet workbook only (IO) or internet workbook plus motivational interview (IMI). In line with prior gambling intervention trials, primary outcomes will include gambling frequency, problem severity, and expenditures, while secondary outcomes will include measures of mental health, time spent on the self-help site, and participant feedback. The hypotheses for the current trial are:

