#### Hypothesis 5 (H5)

The IMI group will demonstrate greater adherence (i.e., more modules completed on the self-help website) compared to the IO group.

In addition to the four hypotheses listed above, one exploratory research question will be examined to determine the impact of each treatment condition on participants’ attitudes toward treatment. Attitudes are important to probe considering common pre-existing reluctance to engage in professional treatment in this population. The following research question will be examined:

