### Sample size estimation

The sample size was determined based on previous work exploring self-directed gambling interventions [11–14] and was computed using G*Power [36] on the basis of H1–H3. The estimation method was based on a repeated-measures between-factors ANOVA, which serves as a simpler derivative of the general linear model that the primary analyses will be based on [37, 38]. Two superiority hypotheses using three primary outcome measures will be analyzed using conventional two-tailed tests with thresholds of power = .80 and *α* = .05. Bonferroni corrections will be calculated to account for multiple comparisons. Correlations of *r* = .50 between baseline and follow-up data were accounted for [16]. A sample size of 108 participants per group will permit statistical detection of small effect sizes (Cohen’s *d* = 0.20 for continuous measures) at the specified significance level. This translates to differential detection of approximately 2 days less gambling per month and a 1-point decrease in NODS scores [37]. After accounting for 20% attrition over 12 months, the resulting planned sample size is 270 participants.

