To aid in clinical significance and translation, H1 and H2 will also be analyzed categorically with two separate logistic regressions. Both analyses will include Group and Time as binary predictors. The analysis to test H1 will include gambling disorder status (meets criteria; does not meet criteria) as the binary outcome. The analysis to test H2 will include recovery status (abstinence; improvement; no improvement) as the multinomial outcome. Improvement is defined as at least a 50% reduction in average number of dollars lost per gambling session.

H3 will be analyzed with a bivariate Pearson correlation between time spent on the site and change in dollars spent per gambling day from baseline to follow-ups.

H4 will be analyzed with two bivariate comparisons. Two unpaired *t* tests will be conducted to determine if the adherence rates differ by group after the 12- and 24-month follow-ups. Adherence will be measured in two ways: (1) number of modules completed on the program and (2) total time spent on the program website.

To test the exploratory research question, bivariate comparisons will be conducted. Q1 will be analyzed with an unpaired *t* test comparing group treatment ratings at each of the follow-up periods (3, 6, 12, and 24 months).

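### The adherence test does not match H5: modules-only adherence is tested under H4 with two measures after two follow-ups, announced as two t tests, with no deciding result

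*Protocol article*

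**What the plan says.** Under Objectives and major research questions, the protocol article gives two specific objectives. The second is to "test the hypothesis that supplemental motivational enhancement increases online self-help treatment adherence and engagement". The matching hypothesis is H5: "The IMI group will demonstrate greater adherence (i.e., more modules completed on the self-help website) compared to the IO group". Adherence there means one thing, modules completed.

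The Data analyses section introduces the adherence test with "H4 will be analyzed with two bivariate comparisons". The next two sentences read "Two unpaired *t* tests will be conducted to determine if the adherence rates differ by group after the 12- and 24-month follow-ups" and "Adherence will be measured in two ways: (1) number of modules completed on the program and (2) total time spent on the program website".

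In the hypothesis list, H4 is a different statement: time on the self-help site correlates with reductions in gambling. The text after H5 counts four hypotheses where five are listed, so the numbering has probably slipped. The result is that no analysis carries the label H5.

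Sample size estimation rests on H1–H3 and describes "using conventional two-tailed tests with thresholds of power = .80 and *α* = .05". It then says that Bonferroni corrections will be made for multiple comparisons, without naming a family or a divisor. The article classes time on the site and the program's user data as secondary outcomes.

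**The concern.** The hypothesis and its test differ in three ways.

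- **Label.** The test is filed under a hypothesis about something else.
- **Definition.** H5 uses modules only. The analysis calls both modules and total site time adherence.
- **Count.** The text announces two tests but names two measures and two follow-ups. The word two could refer to the measures, leaving the deciding time open, or to the times, leaving the deciding measure open. Run in full, the plan gives four results.

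The article has no rule for choosing among these results. Modules and site time may disagree, and so may 12 and 24 months. The two times are also not independent looks. If both measures are cumulative, which is the natural reading of a total time and a number completed, the 24-month value contains the 12-month value. At stake is whether a claim that the interview raised adherence rests on a result fixed in advance or on one picked from up to four.

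**Working it through.** **Inputs from the protocol article**

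- Measures: 2 (modules completed, total site time), Data analyses.
- Times: 2 (after the 12- and 24-month follow-ups), Data analyses.
- Announced tests: 2, Data analyses.
- Two-sided α = .05, Sample size estimation (stated for the primary outcomes).
- Bonferroni: mentioned in Sample size estimation, family and divisor not given.

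The article states no error rate for the adherence tests, so there is no figure of its own to reproduce.

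**Assumptions, not in the article**

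- All four tests are run, and any one significant result is taken as a finding.
- Under no effect, the four test statistics are jointly normal. Their correlation matrix is the Kronecker product of a between-measures matrix (r_m) and a between-times matrix (r_t).
- Main grid: r_t from .70 to .95, r_m from .3 to .7. The article's r = .50 links baseline to follow-up data and does not supply either value.

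**Step 1. Number of comparisons.** 2 measures × 2 times = 4, against 2 announced.

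**Step 2. Independence as the reference case.**

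- Four tests at .05: 1 − .95⁴ = .185.
- Two tests at .05: 1 − .95² = .0975.
- Four tests at .025 (divisor two): 1 − .975⁴ = .096.
- Four tests at .0125 (divisor four): 1 − .9875⁴ = .049.

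**Step 3. Correlated tests.** Chance of at least one significant result among four, from 2 million simulated draws per cell:

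| r_t | r_m | each at .05, two-sided | of which in the IMI direction | each at .025 | each at .0125 |
|---|---|---|---|---|---|
| .70 | .3 | 15.6% | 7.8% | 8.2% | 4.3% |
| .70 | .7 | 13.7% | 6.8% | 7.3% | 3.8% |
| .90 | .5 | 12.6% | 6.3% | 6.7% | 3.5% |
| .95 | .3 | 12.2% | 6.1% | 6.4% | 3.3% |
| .95 | .7 | 10.7% | 5.3% | 5.6% | 3.0% |
| .99 | .3 | 10.7% | 5.4% | 5.5% | 2.8% |
| .99 | .7 | 9.4% | 4.7% | 4.9% | 2.6% |

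The last digit moves by about 0.1 percentage points between runs. The IMI-direction column counts only significant results favouring IMI. Its comparator is 2.5%, half of one two-sided .05 test.

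**Step 4. If only two tests are run.** Unadjusted at .05, the two-sided rate is 6.5% at a correlation of .95 between them, 9.0% at .5, and 9.75% if independent.

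**The case against.** A reader might infer that the plan has a false-positive rate of 11–16% for this objective. The article does not support that. The figure needs four unadjusted tests, an any-hit rule and chosen correlations, and the article states none of these. The Bonferroni sentence neither names nor excludes the adherence tests. With a divisor of four, the rate is below 5%. This part of the objection stands, and the figures here are conditional.

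H5 is directional, so a result favouring IO could not support it. That also stands, and it roughly halves the relevant figure, to about 5.3–7.8% on the main grid. The benchmark then becomes 2.5%, so the relative inflation is similar.

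If the 24-month values largely repeat the 12-month values, the correlation between times may exceed .95. At .99 the two-sided rate is about 9–11%, which is lower but still about twice the nominal level.

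The word two may mean one t test per measure, repeated at each time, since the same section says that analyses are run at 12 and 24 months. That reading is possible, but it yields four tests and still leaves the deciding time and measure open. Site time may be meant for the engagement half of the objective, and modules are listed first. The analysis text nevertheless calls both measures adherence and ranks neither.

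Divisors are often left to an analysis plan, so their absence is not the point. The point is that the printed count is two. A Bonferroni correction built on that count gives 5.6–8.3% on the main grid if four tests are run.

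**Conclusion.** The point holds as an inconsistency within the article. The test of the second specific objective carries the wrong hypothesis label, widens the definition of adherence beyond H5, announces two tests where up to four follow, and names no deciding result.

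The size depends on a reading that the article leaves open. Unadjusted, with any hit counted, the two-sided rate is about 11–16% for the assumed correlations (.70–.95 between times, .3–.7 between measures). It falls to about 9–11% at a time correlation of .99 and rises to 18.5% under independence. A correction for the announced two tests leaves a modest excess over 5%; a correction for four removes it.

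These are secondary outcomes, and the sample size rests on H1–H3. A reader should not conclude that the primary gambling results are compromised, because nothing here bears on them.

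**What to change.** Relabel the analysis H5. State that H5 is decided by a single unpaired comparison of the number of modules completed, which is H5's own definition, at one named time and in all randomised participants, in line with the stated intention-to-treat approach. Twelve months would serve, since it was the last follow-up before the 24-month visit was added by amendment. The article does not dictate 12 over 24 months; what matters is that one is fixed. Report modules at the other time, and site time at both times, as supportive estimates with confidence intervals.

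Alternatively, keep all four comparisons on an equal footing, correct the count to four, and test each at .05 / 4 = .0125.

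Either change takes one or two sentences and no new data. Under the first, site time and the other time point can no longer confirm H5 on their own. Under the second, each test faces a stricter threshold. Recruitment began on 19 August 2020, so the earliest participants had passed 12 months by protocol version 3 (19 October 2021). The choice should therefore be recorded before adherence is compared between groups.

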## Discussion

### Strengths and limitations

Given that most individuals with gambling problems do not seek professional treatment, this intervention’s basis in a stepped-care model is a major strength. In addition to its low intensity, this intervention offers the potential for cost-effectiveness, user-friendliness, and widespread accessibility. Finally, another strength is that gambling severity will be analyzed both continuously and categorically. The categorical analysis classifies participants’ NODS scores (i.e., meets criteria for GD; does not meet criteria for GD) and changes in gambling expenditures (i.e., no improvement; improvement; abstinence). This strategy effectively aids in clinical significance and practical translation of findings by translating raw scores to real-world taxonomies, thereby simplifying the implications of the results.

This study presents with some limitations as well. Of particular importance is the fact that the online program modules can be completed in any order, and not all of the activities must be completed. This program feature does not permit analysis of the degree to which the benefits are conditional upon the order that activities or modules are completed. While user data will still be collected, and some participants may complete the modules in order, there is no way to standardize the order of completion at this time. However, this feature may be viewed as beneficial, since the paper and pencil version of this workbook discussed earlier [10–14] could also be completed in any order; it thereby allows for a more accurate comparison of efficacy between the paperback and online versions. Such comparisons, although imprecise, are important given the absence of a true control group to directly assess program efficacy in this study.

Another limitation is the use of a simplified MI adherence checklist. Best practices recommend much more thorough coding schemes, such as the Motivational Interviewing Treatment Integrity (MITI) protocol. One argument in support of the briefer checklist is that it permits efficient coding of entire interviews. In contrast, more sophisticated integrity protocols are designed to comprehensively code only portions of interviews. Since therapist adherence can fluctuate throughout a single MI session [39, 40], the brief checklist allows for more efficient and representative coding of entire interviews.

## Trial status

Protocol version: 3 (19 October 2021).

Date recruitment began: 19 August 2020.

Approximate date recruitment will be completed: 31 March 2022.

## Data Availability

There are no applicable data since this is a protocol paper. The study materials are available from the corresponding author upon request. The final data resulting from the trial will be accessible to all investigators and available upon request from the corresponding author.

## Abbreviations

AUDIT-C: Alcohol Use Disorders Identification Test – Consumption
DSM-5: Diagnostic and Statistical Manual of Mental Disorders, 5^th^ Edition
GAD-7: Generalized Anxiety Disorder 7-item scale
GPI: Gambling Participation Instrument
IEUQ: Internet Effectiveness and Utility Questionnaire
IMI: Internet plus motivational interview condition
IO: Internet-only condition
K-10: Kessler Psychological Distress Scale
NODS: National Opinion Research Centre DSM-IV Screen for Gambling Problems
PGSI: Problem Gambling Severity Index
PHQ-9: Patient Health Questionnaire 9-item scale
RCT: Randomized controlled trial
SPIRIT: Standard Protocol Items: Recommendations for Interventional Trials
